#### Primary outcome

Breastfeeding rate is the primary outcome in this study. The infant feeding patterns are collected at 1-, 4- and 6-months postpartum. The breastfeeding rate and EBF rate at 1-, 4-, and 6-months postpartum are also calculated.

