## Abstract

**Background:**

Breastfeeding is recognized internationally as the most scientific and effective way to feed infants and young children. According to the World Health Organization in 2022, the exclusive breastfeeding rate within 6 months is 34.1% in China, which is still far from the goal of “more than 60% exclusive breastfeeding rate of infants within 6 months” by 2030 required by China’s State Council. It is necessary to promote breastfeeding and provide maternal breastfeeding guidance to increase exclusive breastfeeding. Factors influencing breastfeeding can be explained by the society ecosystems theory, distributed in macro, mezzo and micro systems. The interventions focused on breastfeeding promotion are mainly carried out in the health systems and services, home and family environment, community environment, work environment, policy environment or a combination of these facilities. But there is sparse research on integrating resources in the macro, mezzo and micro systems of maternal breastfeeding processes to promote breastfeeding behavior. A randomized controlled trial will test the effect of a breastfeeding promotion intervention model based on the society ecosystems theory versus usual prenatal and postnatal care on maternal and infant health and the exclusive breastfeeding rate at 6 months.

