## Methods

### Aim

This study aims to compare the effect of a breastfeeding promotion intervention model based on the SET versus a usual prenatal and postnatal care program on the EBF rate at 6 months and breastfeeding duration; on improving maternal breastfeeding attitudes, knowledge, and self-efficacy; and on improving maternal and infant health.

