### Sample size

The current EBF rate for infants under 6 months of age in China is 34.1% [3]. After the intervention, the rate is expected to increase to 60%, which was required by the *National Nutrition Plan (2017–2030)* [5]. Sample size was calculated for EBR in 6 months for a two-sided hypothesis test with a power of 90% and a significance level of 0.05. Therefore, according to the following formula, the study requires a minimum sample size of 76 (each group). Considering a 20% lost follow-up rate and 20% withdrawal rate because of failure to participate in the full intervention due to prematurity, a total of 218 participants will be needed for the study.$${n}_{1}={n}_{2}=\frac{{{[u}_{\alpha }\sqrt{2P\left(1-P\right)}+{u}_{\beta }\sqrt{{P}_{1}\left({1-P}_{1}\right)+{P}_{2}\left({1-P}_{2}\right)} ]}^{2}}{{(P1-P2)}^{2}}$$

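### The primary outcome fixes neither the rate nor the visit, and does not match the exclusive breastfeeding outcome for which the trial was sized

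*Protocol article*

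**What the plan says.** The Primary outcome section of the protocol article opens with "Breastfeeding rate is the primary outcome in this study". It then says that feeding patterns are collected at 1, 4 and 6 months, and closes with "The breastfeeding rate and EBF rate at 1-, 4-, and 6-months postpartum are also calculated". No visit is singled out, and neither rate is ranked above the other.

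Other sections point to exclusive breastfeeding:

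- The abstract's Background describes a test of the effect "on maternal and infant health and the exclusive breastfeeding rate at 6 months".
- The Aim compares the groups "on the EBF rate at 6 months and breastfeeding duration", followed by attitudes, knowledge, self-efficacy and maternal and infant health.
- The Sample size section starts from "The current EBF rate for infants under 6 months of age in China is 34.1" per cent and continues "After the intervention, the rate is expected to increase to 60" per cent, the target that the Background section gives for EBF. It adds: "Sample size was calculated for EBR in 6 months for a two-sided hypothesis test".

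The Statistical analysis section sets one two-sided 0.05 level and does not name a primary comparison. Its list of between-group analyses covers the morbidity outcomes and the scales but neither breastfeeding rate. EBF appears there only as the subject of a search for influencing factors.

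**The concern.** The primary outcome should be the quantity that the trial was sized to detect. Here the section that defines it uses a broader term than the sample size does. Because the same section names the breastfeeding rate and the EBF rate side by side, the broader term cannot safely be taken as shorthand for EBF.

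Two things are at stake. First, the 90% power was worked out for EBF. No rate or effect for any breastfeeding is assumed anywhere, so the power for that outcome is unknown. Second, with no rate and no visit fixed, a success on the primary outcome could be claimed on any of several comparisons. The components in Table 1 all end by one month postpartum, so the 1-month visit coincides with the end of support, whereas the 6-month visit asks whether the effect lasts. A difference in any breastfeeding at 1 month could be reported as a primary result and leave the 6-month EBF question unanswered.

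**Working it through.** **Which outcome was powered.** Inputs from the Sample size section: P1 = 0.341, P2 = 0.60, two-sided 0.05 (u = 1.960), 90% power (u = 1.2816). The printed formula is n = [u_α √(2P(1−P)) + u_β √(P1(1−P1) + P2(1−P2))]² / (P1−P2)².

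- P = (0.341 + 0.60)/2 = 0.4705, so √(2 × 0.4705 × 0.5295) = 0.7059; times 1.960 = 1.3835.
- √(0.341 × 0.659 + 0.60 × 0.40) = √0.4647 = 0.6817; times 1.2816 = 0.8736.
- n = (1.3835 + 0.8736)² / 0.259² = 5.0946 / 0.0671 = 75.9, rounded up to 76 per group.

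This is the protocol's figure, and power at 76 per group is 90.0%. Both inputs are EBF rates. The abbreviation EBR is not in the abbreviations list; it is read here as the EBF rate because of those inputs.

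**What the primary outcome wording allows.** There are two readings, and only one can hold.

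- *Reading A: any breastfeeding only.* The powered outcome is not the primary one. One rate at three visits gives three comparisons: 1 − 0.95³ = 14.3% if independent.
- *Reading B: both rates.* EBF at 6 months is eligible, and the power calculation applies to that comparison, but it is one of 2 × 3 = 6 with no ranking: 1 − 0.95⁶ = 26.5% if independent.

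The independence figures are upper limits. Exclusively breastfed infants are a subset of breastfed infants at each visit, and the visits share the same infants, so the tests are positively correlated. The document gives no correlation. Simulating six two-sided tests on normal statistics with a common assumed correlation gives:

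| Assumed correlation | Chance of at least one false positive |
|---|---|
| 0.3 | about 24% |
| 0.5 | about 21% |
| 0.7 | about 16% |
| 0.9 | about 11% |

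**After the fix.** With EBF at 6 months as the single primary outcome at two-sided 0.05, n stays at 76 per group with 90.0% power, and the primary test needs no multiplicity adjustment. Keeping all six comparisons primary with a Bonferroni level of 0.05/6 = 0.0083 would need 112 per group before attrition for the same effect; 76 per group would give about 72% power.

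**The case against.** The best defence is that the intention is clear enough: the abstract, Aim and Sample size all point to EBF around 6 months, the first sentence of the Primary outcome section can be an umbrella term, and a statistical analysis plan that is not shown may set the order of testing. An article may also leave detail to a fuller document.

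Part of this stands. A reader might infer that the protocol deliberately chose any breastfeeding and demoted EBF to something merely calculated in addition. The text does not support that: in the closing sentence the word for addition covers both rates equally, and the qualifier any does not appear. A reader might also infer that the power mismatch and the six tests are both established. They belong to different readings. Nor does any section prescribe six confirmatory tests; the count describes what the wording leaves open, and rules on multiplicity are commonly left to the analysis plan. The Aim lists several outcomes besides EBF, and the Sample size section speaks of EBF in or under 6 months, which is not plainly the rate at the 6-month visit.

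What does not stand is the appeal to condensation or to an unseen plan. Condensing explains absent detail. It does not explain a stated primary outcome that differs in its wording from the outcome that was powered.

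**Conclusion.** The point holds as a contradiction within the current text. The primary outcome is not tied to a rate or a visit, and does not match the EBF outcome behind the 76 per group. The size depends on the reading. Under Reading A, power for the primary outcome is unknown and the family-wise error is up to 14.3%. Under Reading B, it is about 16% to 24% at assumed common correlations of 0.7 to 0.3, with 26.5% as a ceiling that nested rates on the same infants would not reach. These error rates assume that every eligible comparison is tested at 0.05 and that any one significant result would be claimed, which the wording permits but does not require. The mismatch itself needs none of these assumptions.

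**What to change.** State in the Primary outcome section that the primary outcome is the exclusive breastfeeding rate at 6 months postpartum, compared between randomised groups at two-sided 0.05. Move EBF at 1 and 4 months, and the breastfeeding rate at 1, 4 and 6 months, to the secondary outcomes with no confirmatory claim. Use the same term in the Sample size section in place of the undefined abbreviation.

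The cost is a few sentences. No new data or participants are needed, and the required 76 per group is unchanged. The change should be made before any outcome is compared between the groups. The downside is that a result on another rate or at an earlier visit can no longer carry the primary claim. The registry entry was not seen and needs changing only if it differs.

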#### Secondary outcomes

##### Maternal and neonatal morbidity outcomes

Maternal adverse lactation events include depressed nipples, breast milk stasis, acute mastitis, cracked nipples, breast swelling, breast eczema, and nipple trauma. The health status of infants will be investigated at 1-, 4- and 6-months postpartum by asking the mothers and their co-parents whether infants suffer from any conditions (eczema, anemia, diarrhea, and pneumonia). The height and weight of the infant at birth, 1 month, 4 months, and 6 months will also be investigated by questioning the mothers and co-parents.

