### Blinding

Allocation details will be placed in opaque and sealed envelopes by a study coordinator and concealed from recruiters, data collectors and the group allocator. After recruitment and baseline data collection, the other study coordinator will open the envelopes and allocated participants. Due to the nature of the intervention, intervention conductors and participants will not be blinded to group allocation. The data collector will be masked to group allocation during data collection and the statistician will also be masked during data analyses.

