	First week after recruitment	** Breastfeeding support facilities:** Pregnant women and those responsible for infant care are introduced to local breastfeeding support facilities, such as mother and baby rooms, Baby Friendly Communities and Hospitals.
	Recruitment to one month postpartum	** To create a good breastfeeding atmosphere:** Actively publicize and report the beneficial experience of breastfeeding through an interactive forum in the Ai You Wei WeChat mini-program; encourage pregnant women and mothers with breastfeeding experience to join the forums and share their experiences and feelings.
Mezzo system (Family)	First week after recruitment	**Join WeChat mini-program:** Invitation to pregnant women and co-parents to join the online platform “Ai You Wei”.
	First and second week after recruitment	** Breastfeeding lecture combined with theories and skills:** Introduce the breastfeeding theory and skills course to pregnant women and co-parents through a combination of online and offline formats. Details of breastfeeding lecture are shown in Table 2.
	First and second week after recruitment	**Course evaluation:** A combination of theory and skills courses to improve breastfeeding knowledge and skills. An online questionnaire at the end of each course assesses the learning of pregnant women and co-parents and provides additional guidance.
Mezzo system (Hospital)	Recruitment to one month postpartum	** WeChat group peer support:** Establish a WeChat group jointly managed by obstetricians and gynecologists, obstetric nurses, midwives, breastfeeding counselors, and community breastfeeding professionals, and invite pregnant women and those responsible for infant care to join the group chat to obtain consultation after recruitment.
	Within 48 h after delivery	** Postnatal hands-on instruction:** Instruct mothers and infant caregivers in obstetrics wards to experience on-site breastfeeding together; insist on early contact, early suckling, and early initiation of breastfeeding; provide instruction on feeding-related skills during hospitalization, including correct feeding positions, milking techniques, and so on.

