Mezzo system (Community)	Seven days, twoweeks and 1-month postpartum	** Home visits:** Researcher and community members conduct postpartum home visits to mothers to provide guidance and education to mothers and those responsible for the upbringing of infants on breastfeeding, diet, exercise, and rest for new mothers, and to improve mothers’ breastfeeding knowledge and skills.
	Delivery to one month postpartum	** Group counseling:** Provide online group counseling (four sessions) to encourage peer-to-peer communication. Mothers’ meetings are organized with the participation of obstetricians and gynecologists, obstetric nurses and researchers, and group discussions are held for mothers and co-parents, who are encouraged to speak out about their inner feelings during breastfeeding.
	Delivery to one month postpartum	**Breastfeeding experience sharing:** Mothers with breastfeeding experience are invited to share the beneficial experience of breastfeeding online every week (four sessions).
Micro system	Recruitment to one month postpartum	**Individual counseling:** One-on-one personalized education or guidance throughout the intervention through home visits, phone calls, and online communication for ongoing breastfeeding.

**Table 2 Tab2:** Schedule of prenatal breastfeeding lectures including theories and skills

	Content
Theory Session 1	1. How is breast milk produced? 2. What factors affect the secretion of breast milk? 3. What are the ingredients in breast milk? 4. What are the characteristics of human milk? 5. What are the benefits of breastfeeding? 6. What do I need to prepare for breastfeeding? 7. How do I breastfeed? 8. How to tell if your baby is full?
Theory Session 2	1. How to prevent and manage common lactation problems? 2. How do mothers with flat or inverted nipples breastfeed? 3. How do mothers with sore or cracked nipples breastfeed? 4. How can breast swelling be prevented and relieved? 5. How do mothers breastfeed when they suffer from infectious/contagious diseases? 6. How should infants and young children be fed under special circumstances? 7. What should mothers eat in lactation period?
Skill Session 1	1. What are the common breastfeeding positions? 2. What are the best positions for babies to latch on to the breast and suckle? 4. What are the ways to promote milk secretion? 5. What are the ways to promote milk reflex? 6. How do I perform breast massage? 7. How do I perform hand milking?

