### Statistical analysis

Statistical analysis will be completed using SPSS (version 24.0). In order to compare the difference at baseline between the two groups, the two-sample t-test will be used for continuous variables and the χ^2^ test for classified data. Analyses of differences between two groups regarding maternal and neonatal morbidity outcomes, IIFAS, BKQ, BSES-SF, PAQ, PSAS-CN, EPDS and SSRS are evaluated in the same manner. In addition, one-way ANOVA analysis and two-sample t-test will be used to explore the influencing factors of the EBF rate. The data from the IIFAS, BKQ, BSES-SF, PAQ, PSAS-CN, EPDS and SSRS of the two groups at different time points (T0, T1, T2 and T3) will be tested using repeated measurement Analysis of Variance (ANOVA). For variables that have an interaction effect in repeated measurement ANOVA, a simple effect analysis will be carried out to further explore the effects of each factor. Cohen’s d will be reported to check the effect size. Cohen’s d will be used to evaluate the magnitude of difference between the two groups. According to the standard established by Cohen, the large, medium and small of the effect of d was divided into 0.8, 0.5, and 0.2 [48]. The randomized trial will use the statistical analysis “per protocol”. The significance level is set to less than 0.05 (double-tailed). P-values will be reported to four decimal places p-values and those less than 0.001 will be reported as p < 0.001.

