The methodological strength of this study is that literature review and qualitative interviews were used during the intervention design of this study to synthesize the experience of previous studies and the actual needs of pregnant women to better support them. This intervention program went through two rounds of expert consensus based on the Delphi method [25], and a total of 12 experts from one university and seven hospitals completed the questionnaire based on the experts’ consensus to assess the importance and rationality of this intervention program. The strengths of the intervention are the addition of appropriate sessions based on the actual needs of the participants and the provision of individualized counseling and guidance. Blixt et al. [64] highlighted the importance of professionals providing evidence-based breastfeeding support in an individualized manner, which may enhance the positive nature of women’s breastfeeding experience.

However, this study will be conducted in only one baby-friendly hospital in a large city in central China, and a multicenter trial cannot be conducted. This might influence the generalizability of the research findings to other regions. Furthermore, due to the social desirability, women who are interested in or willing to breastfeed will participate well in this study, which may result in some biases.

Considering the large disparity in EBF rates between China and the WHO’ recommendations, such a study is needed in order to provide pregnant women with reliable breastfeeding support from the policy system, family, hospital, community and individual levels and provide a reference for countries around the world. This study synthesizes resources at all stages of a woman’s breastfeeding journey to support breastfeeding promotion and provides a new perspective for adding breastfeeding interventions to prenatal and postnatal care for hospital and community healthcare providers.

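### Infant size and anaemia come only from unblinded parents' answers, which adds avoidable error and does not separate untested infants from infants without anaemia

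*Protocol article*

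**What the plan says.** Under Secondary outcomes, in the subsection on maternal and neonatal morbidity, the article names one source for infant size at all four time points, birth included: "The height and weight of the infant at birth, 1 month, 4 months, and 6 months will also be investigated by questioning the mothers". Their co-parents are asked too. Infant illness at 1, 4 and 6 months is obtained by "asking the mothers and their co-parents whether infants suffer from any conditions (eczema, anemia, diarrhea, and pneumonia"). No delivery record, check-up record, study measurement, blood test or diagnostic definition is mentioned there or elsewhere.

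The Blinding section says that "intervention conductors and participants will not be blinded to group allocation"; only the data collector and the statistician are masked. The Statistical analysis section puts these outcomes to formal comparison: "Analyses of differences between two groups regarding maternal and neonatal morbidity outcomes" and the scale scores are to be handled as at baseline, that is, by two-sample t-test or chi-square test.

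On setting, the Discussion states that "this study will be conducted in only one baby-friendly hospital in a large city in central China". Table 1 lists for the intervention arm ward teaching within 48 hours of delivery ("Instruct mothers and infant caregivers in obstetrics wards to experience on-site breastfeeding together") and later home visits ("Researcher and community members conduct postpartum home visits to mothers"). Controls have usual care and no further guidance.

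**The concern.** Infant health is part of the stated aim, and height and weight are the only growth measures. Three features of the chosen source are weak.

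- **Birth size.** Weight and length at birth would be expected in a maternity hospital's own record. Asking parents instead accepts reporting error that could probably be avoided.
- **Size at 1, 4 and 6 months.** A value given by a parent may be remembered, rounded or measured some time before the contact. The article does not say that its source or date is noted.
- **Anaemia.** Unlike diarrhoea, anaemia is not something that a parent reliably sees. As described, the question puts an infant tested and found normal in the same group as one never tested.

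Error unrelated to arm widens the variance of size and shrinks any difference in anaemia. If reporting or testing differed between arms, the comparison would be biased, and masking the data collector would not help because the error arises with the informant.

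**Working it through.** **The plan's own figure.** The article gives no calculation for infant size or anaemia. Its only sample-size figure concerns exclusive breastfeeding and supplies the number per arm used below. Inputs from the Sample size section: P1 = 0.341, P2 = 0.60, two-sided alpha 0.05, power 90%. Mean P = (0.341 + 0.60)/2 = 0.4705.

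n = [1.96 × √(2 × 0.4705 × 0.5295) + 1.2816 × √(0.341 × 0.659 + 0.60 × 0.40)]² / 0.259² = (1.3835 + 0.8736)² / 0.0671 = 75.95, so 76 per group. This reproduces the plan. Then 76 × 1.2 × 1.2 = 109.4, taken as 109 per group, or 218 in total.

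Everything below uses 76 per arm and two-sided 0.05. **All SDs, error SDs, reliabilities, rates, sensitivities and specificities are assumptions, not figures from the article.**

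**Infant size, in units.** The difference detectable with 80% power is (1.96 + 0.84) × SD × √(2/76) = 0.454 × SD. With reporting error, SD becomes √(SD² + error SD²).

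| Measure at 6 months | True SD | Error SD | Variance increase | Observed SD | Detectable difference |
|---|---|---|---|---|---|
| Length, cm | 2.3 | 0 | none | 2.30 | 1.04 |
| Length, cm | 2.3 | 1.5 | 2.25/5.29 = 43% | 2.75 | 1.25 |
| Length, cm | 2.3 | 2.0 | 4.00/5.29 = 76% | 3.05 | 1.38 |
| Weight, kg | 0.8 | 0 | none | 0.80 | 0.36 |
| Weight, kg | 0.8 | 0.3 | 0.09/0.64 = 14% | 0.854 | 0.39 |

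**Infant size, in power.** With reliability r, a true standardised difference of 0.5 is observed as 0.5 × √r. Power is 87% at r = 1, 83% at 0.9, 79% at 0.8 and 73% at 0.7.

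**Anaemia, same error in both arms.** The observed rate is sensitivity × p + (1 − specificity) × (1 − p). Take true rates of 20% and 10% and, outside the error-free row, specificity 0.98.

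| Sensitivity | Observed rates | Difference (points) | Power |
|---|---|---|---|
| 1, with specificity 1 | 20.0% v 10.0% | 10.0 | 41% |
| 0.7 | 15.6% v 8.8% | 6.8 | 25% |
| 0.5 | 11.6% v 6.8% | 4.8 | 17% |
| 0.3 | 7.6% v 4.8% | 2.8 | 11% |

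**Anaemia, error differing by arm.** Take a true rate of 20% in both arms and specificity 0.98. Sensitivity 0.5 v 0.7 gives observed rates of 11.6% v 15.6%, and the test rejects about 11% of the time instead of 5%. Sensitivity 0.4 v 0.7 gives 9.6% v 15.6% and about 20%. These figures show what differential reporting would do, not that it will occur.

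**The case against.** The strongest reply is that much of this rests on inference.

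- **Record access.** Recruitment is at one hospital, but the article does not say that every woman delivers there or that the data collector may open clinical records. The ward teaching in Table 1 concerns the intervention arm only. This stands, so parental report must remain as a fallback.
- **Later visits.** Parents may already read values from a check-up record, and questionnaire detail is commonly left out of an article. This also stands: the error at 1, 4 and 6 months may be smaller than illustrated. Parental answers nevertheless remain the only stated source.
- **Size of the gain.** The comparator above is error-free, whereas recorded values also carry error. The length result depends wholly on an assumed error of 1.5 to 2.0 cm, and weight moves only from 0.36 to 0.39 kg. Birth size itself is not quantified.
- **Differential testing.** A reader might infer that intervention infants will be tested more and so show more anaemia. The article does not support that. All contacts in Table 1 end by one month postpartum, none includes a blood test, and anaemia is asked again at 4 and 6 months.
- **Anaemia among tested infants.** A reader might take this rate as the cleaner comparison. Testing happens after randomisation, so the tested subsets need not be comparable; reporting the tested share discloses that problem without removing it.
- **Adjustment.** A reader might also infer that poor birth data spoil a planned growth adjustment. None is stated, and weeks of delivery are already collected.

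What survives is the core: a weaker source is fixed in the text where better information is probably within reach, and no category is described for infants not tested.

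**Conclusion.** The point holds as a modest, low-cost improvement. Parental questioning is the only stated source for infant size and anaemia, the informants are unblinded, and the outcomes are tested between arms. The result is avoidable measurement error, and an anaemia outcome that cannot separate not tested from not anaemic.

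The case is clearest for birth size and for anaemia. The size of the loss cannot be derived from the document; the calculations show direction and plausible scale only. Bias between arms is possible but not shown. Only secondary outcomes are affected: the primary outcome, the 76 per group and the total of 218 stand.

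**What to change.** 1. **Birth weight and length:** take them from the delivery record where the birth was at the study hospital. Elsewhere use parental report, flagged as such.
2. **Size at 1, 4 and 6 months:** ask parents for the most recent recorded measurement and its date where they have one, note the source, and account for actual age in the analysis.
3. **Anaemia:** ask whether it was found by a blood test or a clinician's diagnosis, and keep not tested as a separate category. Compare parent-reported diagnosed anaemia among all randomised infants with data, showing the tested share by arm. Treat any tested-only rate as descriptive. The article's announced per-protocol analysis is a separate question, but this comparison should not be narrowed further to tested infants.

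The cost is a record look-up by the existing data collector and a few questionnaire fields. No new visit or test is needed. The downside is mixed sources for births elsewhere, so the source should be tabulated by arm. Access to records should be confirmed first.
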